### 2.3 Comparative analysis

Qualitative variables will be compared between the groups with the  $\chi^2$  test or the corrected  $\chi^2$  or non-parametric Fisher's exact test, according to the values of expected frequency under the independence assumption. A logistic or polytomic model will be used to consider adjustments if necessary. The assumption of log-linearity of the association will be systematically checked.

Quantitative variables will be compared between 2 groups of intervention by Student t test if the conditions of validity are respected (normal distribution, homogeneous variances). If the variances are unequal between the 2 groups, a t-test for unequal variances will be used, if the distribution is not normal, a non-parametric Wilcoxon test will be used.

A linear regression model will be used to adjust on variables if necessary. The assumption of linearity of the association will be systematically checked. The other assumptions of the model (normality and homoscedasticity of residuals) will be studied. A transformation of the quantitative variable may be considered if necessary.

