### Methods for randomization:

The randomization list will be established by the biostatistician of the Centre de méthodologie et de gestion (EUCLID, CHU Bordeaux, France and Inserm, F-CRIN platform) before the beginning of the research. The allocation of the intervention will be done according to a 1:1:1 ratio.

- Group 1: Meditation
- Group 2: Learning a foreign language (English)
- Group 3: Passive control (follow-up without intervention)

A document describing the randomization procedure will be kept confidential by the EUCLID Statistician. The randomization of the participants will be done before the beginning of the intervention by the investigator in a centralized way via the Ennov Clinical software. This centralization allows the investigator and possibly other correspondents to be informed of the randomization of each participant. From the second wave onwards, the foreign language learning group will be divided into 2 subgroups in order to respect the logistic constraints on group size. The allocation in each of the two English groups will be drawn at random, and adapted by the English teachers if necessary from the level assessed during the English test carried out during the diagnostic battery, to limit the heterogeneity of level within the same group.

Assignment of the non-medical senior intervention is unbeknownst to the individuals responsible for data analysis for all visits, including visit 4.

The investigating team (medical investigators, neuropsychologists, radiological manipulators, nuclear physicians) knowing the identity of the participants is not the one who analyses the data.

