## **6.7. Randomization (Non-expert seniors only)**

Once all inclusion visit examinations have been completed for the entire wave (i.e., 42 participants for Wave 1 and 54 participants for Waves 2 and 3), participants will be contacted by telephone by one of the protocol investigators to confirm the planned start date of the intervention (Visit 2) within the next 2 weeks and to ensure that the participant still wants to participate in the trial prior to randomization. If the participant confirms their attendance, then the investigator can proceed to the randomization of the participant. To do so, they log into the e-CRF, complete the "randomization" page with the eligibility criteria and validate the content. The site immediately displays the group allocated to this participant.

If unable to connect to the e-CRF, the investigator will contact the Euclid platform.

The result of this randomization will be communicated to all participants in the same session at the same time shortly before the start of the intervention in order to limit the risk of participants dropping out if they were not assigned to the group they wanted (although this risk should be limited as early as the participant selection phase). Information will be communicated both by telephone and by mail (including important information about the first sessions of the intervention programs for participants assigned to the meditation and foreign language learning groups).

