## **6.8. 18-month intervention**

As mentioned above (6.7. Visit 1 - Inclusion Visit), the inclusion of the non-expert senior participants will be conducted in three waves of participants (divided into three arms). The waves will be spaced approximately 6 months apart. Interventions will therefore also begin in three waves spaced approximately 6 months apart, and all intervention groups will consist of 14 participants.

Participants will be asked not to engage in the proposed activity in the arms to which they have not been assigned for the duration of the intervention. Participants assigned to the meditation group and the foreign language group will have a standardized intervention program following a well-defined plan described in a detailed manual (for the meditation intervention) or following a specific program (for the foreign language intervention) lasting 18 months. Both interventions will be delivered by experienced and motivated teachers. The formats of the interventions will be identical in terms of the volume and frequency of sessions, home practice, and group exchange periods. The number of teachers per class and their level of expertise in delivering these programs will be identical between the interventions.

Thus, for both types of intervention, participants will have:

- Group classes of 2 hours, once a week,
- Exercises to be done every day for at least 20 minutes,
- More intensive days and/or half-days of practice.

In each weekly group session, there will be a time for presentation, a time for sharing, and a time for practice; the first two sessions of each month will include an equal amount of these three aspects (3x40min), session 3 will include more sharing (30/60/30min), and session 4 more practice (30/30/60). For each intervention, participants will be provided with supports (manual and audio) for their practice. The alternation of supports (texts, images, audio, video) and activities (alone, in pairs, in groups) will contribute to maintain interest and motivation.

Participants will be strongly encouraged to participate in all of these activities over the course of the intervention (18 months). In addition, they will be given a questionnaire at the beginning of the intervention to assess their expectations of the intervention (Credibility/Expectancy questionnaire, Devilly et al., 2000).

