### 11.2. *Calculation of the study size*

#### Study on non-expert seniors:

The comparison between the meditation group and the no-intervention group is going to focus on the difference in 1) volume and 2) perfusion of the anterior cingulate cortex 18 months after the start of the intervention compared to the value at inclusion, with an expected effect size of 0.75 (effect size of short-term meditation vs. no intervention, from a meta-analysis on the effects of meditation on brain imaging markers: Fox et al, 2014). Given that the intervention in the current protocol is 18 months, we consider that the effect size will be at least equal to 0.75.

The same effect size of 0.75 is expected for the comparison between the meditation group and the English learning group on the difference in 1) insula volume and 2) insula perfusion 18 months after the start of the intervention compared with the inclusion value.

To show an effect size of 0.75 for each comparison, with 80% power and a two-sided first-species risk of 1.25% (Bonferroni correction because four comparisons will be performed) 42 participants per group must be recruited for a total of 126 participants.

Assuming that the effect size assumptions are conservative and that precautions are taken at the time of recruitment to best ensure adherence of participants to the trial, we expect that the risk of dropout after knowledge of the randomization group is very low and that the power of the study is preserved. However, we will implement close monitoring of these refusals at the beginning of the trial. In order to increase the statistical power of the secondary analysis on the FDG-PET examination carried out from

the second wave of inclusion, 24 participants will be recruited in addition, i.e. 8 additional participants per group (meditation, English, passive control) for a total of 150 participants.

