### **For the randomized clinical trial with non-expert seniors:**

The comparison of the meditation vs. no intervention arms will focus on the change in 1) volume and 2) metabolism of the anterior cingulate cortex from baseline to the end of the 18-months intervention, with an expected effect size of 0.75.

We expect the same effect size of 0.75 for the comparison between the meditation arm and learning of English arm on the change in 1) volume and 2) metabolism of the insula from baseline to the end of the 18-months intervention.

To demonstrate an effect size of 0.75 for each of the four comparisons, with 80% power and a two-sided type I error of 1.25% (Bonferroni correction for test multiplicity), 42 participants per arm need to be included for a total of 126 participants.

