#### 2.1.3 Type I error rate

The statistical tests for the main objectives (1 + 1bis) will be performed with 1.25% error rate each, controlling the family-wise error rate to 5% for the 4 comparisons.

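### The primary test treats participants as independent although both active arms are taught in a handful of classes, so the stated 1.25% and 5% error rates assume no class or teacher effect specific to an arm

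*Combined protocol and SAP*

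**What the plan says.** Section 2.3 of the primary SAP sets the test: "Quantitative variables will be compared between 2 groups of intervention by Student t test if the conditions of validity are respected". An unequal-variance t test or a Wilcoxon test is the fallback. All three work on individuals and assume independence. Section 3.6.1 adds an adjusted version with age, education, gender and MMSE. Neither the primary nor the secondary SAP puts class, teacher or wave in a model.

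On error control, section 2.1.3 of the primary SAP says the tests for the main objectives "will be performed with 1.25% error rate each, controlling the family-wise error rate to 5% for the 4 comparisons". Its sample size paragraph says that, "with 80% power and a two-sided type I error of 1.25% (Bonferroni correction for test multiplicity), 42 participants per arm need to be included". Protocol section 11.2 gives the same figure and then raises the total to 150, which is 50 per arm. Neither place mentions an ICC or a design effect.

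On delivery, protocol section 6.8 describes weekly two-hour group classes over 18 months in both active arms, starting in three waves about six months apart. Section 6.7 sizes the waves as "42 participants for Wave 1 and 54 participants for Waves 2 and 3", and section 3.2 says "The allocation of the intervention will be done according to a 1:1:1 ratio". From the second wave, section 3.2 adds, "the foreign language learning group will be divided into 2 subgroups in order to respect the logistic constraints on group size"; teachers may then alter the random draw according to English level. Yet section 6.8 also says "all intervention groups will consist of 14 participants".

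**The concern.** People who share a class share a teacher, a pace and a group for 18 months. The protocol itself gives reasons to expect some class effect: meditation teachers adapt their teaching to what participants report (6.8.1), English subgroups may be re-sorted by level (6.8.2), and the quality of social ties within the group is measured (10.1.3).

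If the average result differs from class to class within an arm, that variation is part of the uncertainty about the intervention's effect. A t test on individuals leaves it out, and with so few classes it does not average away. Standard errors are then too small and the test rejects more often than stated. All four primary tests share this exposure: meditation is clustered in each, and English is clustered in the two insula tests.

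Wave is a separate matter. Differences in 18-month change between waves (scanner drift or season, for example) are explainable variance that the plan leaves in the error term.

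**Working it through.** **The plan's own figure.** For d = 0.75, two-sided alpha 1.25% and independent observations, the exact noncentral t gives 79.7% power at 41 per arm and 80.9% at 42. So 42 per arm is right, under independence. At 50 per arm the power is 88%.

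**Class structure (derived, not stated).** Waves of 42, 54 and 54 at 1:1:1 give 14, 18 and 18 per arm. If meditation stays as one class per wave, its classes are 14, 18, 18. If English halves equally from wave 2, its classes are 14, 9, 9, 9, 9.

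**Effective class size**, Σm²/Σm:
- meditation: (196 + 324 + 324)/50 = 16.88
- English: (196 + 4 × 81)/50 = 10.4
- passive: no clustering

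**Design effect per arm**, 1 + (effective size − 1) × ICC. At an ICC of 0.05:
- meditation: 1 + 15.88 × 0.05 = 1.794
- English: 1 + 9.4 × 0.05 = 1.47
- passive: 1

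**Variance inflation of the difference** (equal arms, so the mean of the two design effects):
- meditation vs none: (1.794 + 1)/2 = 1.397, square root 1.18
- meditation vs English: (1.794 + 1.47)/2 = 1.632, square root 1.28

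The true standard errors are 1.18 and 1.28 times the reported ones. The reported ones are therefore too small by 1 − 1/1.18 ≈ 15% and 1 − 1/1.28 ≈ 22%.

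**True alpha** = 2 × (1 − Φ(2.498/√inflation)), where 2.498 is the two-sided 1.25% critical value. The ICC is an assumption.

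| ICC | Inflation, vs none / vs English | True alpha, vs none / vs English | Sum over four tests |
|---|---|---|---|
| 0 | 1.000 / 1.000 | 1.25% / 1.25% | 5.0% |
| 0.01 | 1.079 / 1.126 | 1.6% / 1.9% | 7.0% |
| 0.02 | 1.159 / 1.253 | 2.0% / 2.6% | 9.2% |
| 0.05 | 1.397 / 1.632 | 3.5% / 5.1% | 17.0% |
| 0.10 | 1.794 / 2.264 | 6.2% / 9.7% | 31.8% |

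The last column is a Bonferroni upper bound on the family-wise error, not an estimate of it.

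**Simulation of the planned t test** (100,000 trials per setting) agrees: 2.1% / 2.6% at an ICC of 0.02, 3.5% / 5.1% at 0.05, 6.2% / 10.0% at 0.10.

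**Sensitivity to the class structure, ICC 0.05.**
- 14 per arm per wave, English 14, 7, 7, 7, 7: simulated 3.0% / 4.3%.
- Meditation split as English is: inflation (1.47 + 1)/2 = 1.235 and 1.47, so about 2.5% / 3.9%.

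**Wave alone.** With a wave effect common to the arms, equal arm sizes within each wave and no class effect, simulated alpha for meditation vs none is 1.1%, 0.9% and 0.9% at wave variances of 0.05, 0.10 and 0.20 (within-arm variance 1). The test becomes slightly conservative.

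**Class sizes.** 54/3 = 18 per arm, and half of 18 is 9. Neither is the 14 given in section 6.8.

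**The case against.** The strongest reply is that participants are randomised individually. If the interventions change nobody's outcome, the test is valid however the classes are arranged. This stands: the inflation concerns the null of zero average effect with effects that differ between classes. That is the null that matters for inference beyond these particular teachers and groups, but it is a narrower claim than a general failure of the test.

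Next, nothing in the documents supports any particular ICC. The outcomes are change in regional MRI volume and early-frame PET, acquired on the same scanners, with blinded evaluators, standardised programmes and monthly meetings with teachers. The ICC could be close to zero. This also stands. Class effects are more plausible for the self-report composite that is the main secondary outcome, where both compared arms are clustered.

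Third, the class structure is inferred. No section says that meditation ran as one class of 18 or that English divided equally. The alternatives above change the figures but not the direction.

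Three stronger readings are tempting and are not supported. A reader might infer that omitting wave itself inflates type I error; with balanced arms it does not. A reader might infer that the pandemic disturbed wave 3's primary data. But section 3.3 puts the last V4 in June 2022 (± 6 months), 29 months after the V3 period, so V3 ends around January 2020, before the lockdown of 17 March 2020. And a reader might infer that unequal class sizes break the promise of identical formats; section 6.8 promises equal session volume and frequency, home practice, exchange time, and teacher numbers and expertise, but not equal class size.

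**Conclusion.** The point holds in limited form. The 1.25% and 5% error rates, and the 80% power at 42 per arm, rest on an unstated assumption that there is no arm-specific class or teacher effect. If the class ICC is zero, the plan delivers what it claims. With the derived classes, even 0.01 moves a nominal 1.25% test to 1.6% or 1.9%, and 0.05 moves it to 3.5% or 5.1%. The documents cannot say where in the range of 0 to 0.10 the truth lies, so this does not show that the trial's error rate is wrong, only that the plan neither checks nor states what it depends on. Wave is a precision issue. Independently of any ICC, the group size of 14 in section 6.8 cannot be squared with waves of 54 and a divided English arm.

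**What to change.** 1. Add wave as a fixed effect to the adjusted regression in section 3.6.1 of the primary SAP and to the Objective 2 and 3 models in the secondary SAP. The cost is two degrees of freedom. The unadjusted two-group test can stay as written.
2. Prespecify a partially nested sensitivity model: a random class effect in the active arms only, with small-sample degrees of freedom, and the class ICC reported with its interval. Record each participant's final class after any teacher reassignment; the documents describe the initial English draw in the eCRF but not whether later changes are kept. State that the model is imprecise. Meditation vs English would have about 3 + 5 − 2 = 6 degrees of freedom, and power at d = 0.75 of about 55%, 50%, 38% and 27% at ICCs of 0.01, 0.02, 0.05 and 0.10. It is therefore unsuitable as the primary analysis.
3. Qualify section 2.1.3 of the primary SAP and section 11.2 of the protocol to say that the error rate and the 80% power assume no class effect, with a short table over a range of ICCs.
4. Reconcile the group size in protocol section 6.8 with the wave sizes in 6.6 and 6.7 and the English subgroups in 3.2 and 6.8.2.

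Apart from recording final class membership, this is SAP and protocol wording.

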### 2.4 Calculation conventions for statistical analysis

#### 2.4.1 Conventions for time calculations

- Time between 2 dates **in months** =  $\frac{(\text{Date 2} - \text{Date 1})}{30.4375}$
- Time between 2 dates **in years** will be estimated as the number of year between two dates. The function "YRDIF" of SAS will be used with the "Actual" option.

Convention for dates: Except in special cases, if the day is missing, the convention is to use the value "15", i.e. mid-month. If the day and month are missing, the convention is to use the value "1" for days and the value "7" for month, i.e. mid-year. This convention allows us to measure time estimates. The biostatistician makes these imputations at the time of analysis and consistency is checked at the time of data review.

#### 2.4.2 Conventions for the calculation of the change (delta) of measurement between 2 visits

The difference between two measurements, one taken at D00 and a second taken at a visit posterior to D00 (follow-up visit DXX) will be calculated using the following formula:

- Delta = (measurement at DXX – measurement at D00)

#### 2.4.3 Conventions for BMI calculations

- $$\text{BMI} = \frac{\text{Weight (kg)}}{\text{Height}^2 \text{ (m)}}$$

#### 2.4.4 Conventions for handling missing data

The following values are used in the database to describe the missing data:  
– « NK » or « K »: Unknown

## STATISTICAL ANALYSIS PLAN

- « ND » or « D »: Not done
- « NA » or « A »: Not applicable

There will be no distinction in the statistical analyses according to the type of missing data.

### 2.5 Software used

The analyses will be performed using SAS® software (version 9.3 or higher).

### 3. Analysis plan

---

#### 3.1 Description of randomization

- Description of the method of randomization: size of blocs, fixed or random method...
- Description of the deviations of randomization

#### 3.2 Description of protocol deviations

For all eligibility criteria (inclusion and non-inclusion), the biostatistician will check that the inclusion criteria is “yes” and the non-inclusion criteria is “no” in the corresponding SAS table. Additional verifications can be made if needed.

The other following deviations are described per category:

- Randomized participants who did not receive the trial intervention
- Participants who received the wrong intervention
- Participants who received a forbidden concomitant treatment. The following therapies should be avoided: psychotropic drugs, antihistamines, anti-Parkinsonian drugs, benzodiazepines, non-steroidal anti-inflammatory agents, antiepileptics, analgesic drugs and muscle relaxants (see exclusion criteria)

Deviations per participant are described.

#### 3.3 Description of enrolment and follow-up

- Participant enrolment and follow-up are described based on the study profile as defined in the CONSORT recommendations (3). According to CONSORT diagram,
  - Participants assessed for eligibility (n)
  - Participants excluded and reasons (n, %)
  - Participants randomized in total and in each group (n, %)
  - Participants having received the trial intervention (n, %)
  - Participants who did not received allocated intervention (n, %)
  - Participants lost to follow-up (n, %)
  - Participants to include in the analysis (n, %)
  - Participants to exclude from the analysis and reasons (n, %)
- Review of the database: number of records in each table

#### 3.4 Participants' characteristics

The following characteristics are described for all enrolled participants overall and per group.

##### 3.4.1 At enrolment

- Socio-demographic characteristics
  - Gender
  - Age (years)
  - Level of education (in number of years from the 1st year of school = CP in France)
  - Number of years in retirement
  - Memory Complaint (score at MacNair)
  - Familial history of AD (percentage yes)

## STATISTICAL ANALYSIS PLAN

- Clinical characteristics
  - Diastolic and systolic blood pressure (mmHg)
  - Height (m), weight (kg) and BMI (in kg/m^2, in classes)
  - Hip and waist circumferences (cm)
- Diagnostic battery test
  - Laterality-Edinburgh
  - MMSE
  - MADRS
  - Grober and Buschke (FR1+FR2+FR3)
  - Modified (Wisconsin) Card Sorting Test
  - English test

### 3.4.2 At the end of the trial

- Death
- Compliance
  - Total number of classes attended
  - Total number of reported practice sessions
  - Total number of minutes of formal practice
  - Total number of minutes of informal practice
- Adverse events
  - Severity
  - Relationship to the study intervention or radiopharmaceutical drugs

## 3.5 Partners' characteristics

- Socio-demographic characteristics
  - Gender
  - Age (years)
  - Relationship to participant
  - Live with participant (Yes/No)
  - Number of years knowing the participant
  - Number of hours per week spent with the participant

## 3.6 Analysis of trial objectives

### 3.6.1 Primary objectives (Objectives 1 and 1bis)

The difference between two measures will be calculated with the following formula:

